### 10.2 Secondary Objective: To determine the durability of efficacy of SARS-CoV-2 rS/M1 vaccine against infection

Endpoint: SARS-CoV-2 detected by RT-PCR on self-collected SNIFF-provided nasal swabs, right-censored at the last negative RT-PCR test at or before the earliest of termination or receipt of EUA vaccine.

Data set: Post crossover analyses set (PCAS)

Approach: The analyses for the primary endpoint will be repeated with the time origin being time of second dose (placebo or active) in the crossover series. Durability will be assessed through a time-invariant hazard ratio with supporting analyses investigating evidence of non-proportionality of the hazards that could indicate loss of efficacy in the early vaccination arm. The study may not be adequately powered for this analysis. Evidence will also be supported by the data that will be presented in the mock table (Table 1 in this document) which will examine incidence rates over calendar time in both randomization arms.

If there is adequate power, the supporting analysis for the primary objective will be repeated for this objective.

### 10.3 Secondary Objective: To determine the durability of efficacy of SARS-CoV-2 rS/M1 vaccine against asymptomatic/very mildly symptomatic infection

Endpoint: SARS-CoV-2 detected by RT-PCR on self-collected SNIFF-provided nasal swabs, right-censored at the last negative RT-PCR test at or before the earliest of: a COVID-defining endpoint from the parent trial, termination or receipt of EUA vaccine.

Data set: Post crossover analyses set (PCAS)

Approach: The analysis in section 10.2 will be repeated for this outcome.

## 11. EXPLORATORY ENDPOINTS

This section describes the planned analyses for exploratory endpoints. As appropriate for exploratory endpoints, we expect that these analyses will be supported by ad hoc analyses as suggested by the data.

### 11.1 Exploratory Objective: To determine the sequence of breakthrough SARS-CoV-2 infections

*SARS-CoV-2 Genome Sequence Analysis* – Samples with “detected” interpretations by the N1/N3 SARS-CoV-2 assay will be referred for additional screening and whole genome sequencing. Samples with N1 cycle threshold values (Ct) of  $\leq 32$  will be prepared for whole genome sequencing. Samples with Ct

values > 32 will be evaluated according to their likelihood to generate a quality genome sequence to maximize the number of viral genomes from unique research participants. The genomic data will be analyzed to produce a pangolin lineage call (ex. B.1.1.7) and Greek alpha label (ex. Alpha) as applicable for variants of interest/concern.

### **11.2 Exploratory Objective: To estimate the VE on duration of infection**

Endpoint: Duration of shedding as indicated by RT-PCR as measured by the number of RT-PCR positive swabs. If a swab is missing between two RT-PCR positive swabs, it will be treated as if it were RT-PCR positive. If there are missing swabs just before the first or after the last RT-PCR positive swab, the endpoint will be interval censored with the interval being: (number of RT-PCR positive swabs, number of RT-PCR positive swabs + number of missing adjacent swabs).

Data sets: PP-ITT, PP-PAS, PP-PAS2

Approach: A Poisson model will be fit with randomization arm as the predictor of interest. Covariates will be included to account for potential post-randomization selection bias. These will include sex, age, and presence of comorbidities measured at the time point closest to but before infection.

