## 6.5 Final Study Visit

The final ancillary study swab will be collected by December 17, 2021 at which point the participant's ancillary study participation will be completed (Appendix).

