### 3. GENERAL DATA ANALYSIS CONSIDERATIONS

#### 3.1 Analysis Set(s)

For analysis purposes, the following populations are defined:

**Intention to Treat (ITT):** All enrolled participants who had at least one valid result in the lab results dataset

**Modified Intention to Treat (mITT):** All ITT participants who were not identified as having SARS-CoV-2 infection, either through RT-PCR or serological testing, prior to administration of the second dose of the first dosing series.

**Primary analysis set (PAS):** The intention of the SNIFF protocol was to enroll participants at their second dose of the first vaccination series and immediately start swabbing. This would allow exclusion of all participants who were previously infected. However, many participants enrolled after the second dose of the initial series, and it may be impossible to determine if they acquired infection in between that second dose and the first swab. We define this data set to account for this by limiting inclusion to mITT participants enrolled before 4 weeks post second dose of the initial series. Primary analyses will be conducted on this data set.

**Primary analyses set 2 (PAS2):** All mITT participants enrolled by July 12, 2021. Primary analyses will be conducted on this data set. This analysis set serves as a complement to PAS in case too many participants have enrolled after 4 weeks post second dose of the primary series. 82.4% were enrolled by this date.

**Post crossover analysis set (PCAS):** All mITT participants enrolled before 4 weeks post second dose of the crossover series without evidence of prior infection before or at the second dose of the crossover series.

**PCR-positive (PP-ITT):** All participants in the ITT population with SARS-CoV-2 RNA detected by RNA-RT-PCR as part of the SNIFF study (as determined by the lab).

**PCR-positive PAS (PP-PAS):** All participants in the PAS with SARS-CoV-2 RNA detected by RNA-RT-PCR as part of the SNIFF study (as determined by the lab).

**PCR-positive PAS (PP-PAS2):** All participants in the PAS2 with SARS-CoV-2 RNA detected by RNA-RT-PCR as part of the SNIFF study (as determined by the lab).

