### **11.3 Exploratory Objective: To estimate the VE against SARS-CoV-2 viral load as a proxy of transmission**

Endpoint: Peak viral load (and subgenomic RNA, if tested), as a proxy for transmission, in RT-PCR positive swabs

Data sets: PP-ITT, PP-PAS, PP-PAS2

Approach: Linear regression summaries of the peak viral load on the log10 scale will be used with vaccination status (no vaccine, 1 dose, 2 doses) as the covariate of interest, adjusted for age and sex.

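### SAP 11.2 and 11.3 analyse infections already under way at the first swab, and runs still positive at the last, as fully observed; PP-ITT is affected most

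*Supplement*

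**What the plan says.** SAP v2.0 section 11.2 measures duration as the number of RT-PCR positive swabs. A gap inside a positive run is filled as positive. Uncertainty at the edges is recognised in one case only: "If there are missing swabs just before the first or after the last RT-PCR positive swab, the endpoint will be interval censored", with an upper limit equal to the positives plus the missing neighbours. The model is brief: "A Poisson model will be fit with randomization arm as the predictor of interest". Section 11.3 takes "Peak viral load (and subgenomic RNA, if tested), as a proxy for transmission, in RT-PCR positive swabs" and regresses it on the log10 scale, "with vaccination status (no vaccine, 1 dose, 2 doses) as the covariate of interest", adjusted for age and sex. It has no rule for an infection that was only partly sampled.

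Both sections use the same sets: "Data sets: PP-ITT, PP-PAS, PP-PAS2". PP-ITT is "All participants in the ITT population with SARS-CoV-2 RNA detected by RNA-RT-PCR as part of the SNIFF study" (section 3.1), and ITT is "All enrolled participants who had at least one valid result in the lab results dataset". The exclusion of infection found by RT-PCR or serology before dose 2 enters only at mITT, from which PAS and PAS2 are drawn.

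Three further points fix the observation window. The footnote to Supplement Table S3 counts a collection window as expected only from enrolment to discontinuation. Protocol v4.0 section 6.5 sets a common end: "The final ancillary study swab will be collected by December 17, 2021". Protocol section 5.1.1 requires two doses of study product before enrolment.

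**The concern.** Duration and peak can be read from a swab series only if the series covers the start of the infection and, for duration, its end. An infection already under way at the first swab shows a shortened count and possibly only the falling part of the viral-load curve. Under the SAP both are analysed as complete.

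The error need not cancel between arms. Infection acquired before protection begins should be about equally frequent per participant in both arms, while later infection is reduced by the vaccine. Carried-over infections are then a larger share of vaccine-arm positives. Since two doses precede enrolment, residual RNA from a vaccine-arm infection acquired before dose 2 is analysed under two doses. Protocol section 2.2.1 treats magnitude and duration of shedding as proxies for transmission potential, so a spurious difference would be read as a vaccine effect on transmission.

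**Working it through.** **Inputs.** From Supplement Table S2, mITT censored at crossover dose 2: vaccine 16 infections, 628 participants, 110.3 person-years; placebo 28, 302 and 50.1. From Table S3: 28489 of 45252 expected windows filled.

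**Reproducing the stated figures.** The SAP gives no power or effect size for 11.2 or 11.3, so the check is on the inputs.
- Vaccine: 16/110.3 x 100 = 14.5 per 100 person-years, exact Poisson 95% CI 8.3 to 23.6 (stated 14.5; 8.3, 23.5).
- Placebo: 28/50.1 x 100 = 55.9, CI 37.1 to 80.8 (stated 55.8; 37.1, 80.7).
- Completion: 28489/45252 = 63.0%, as stated.

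The differences are rounding of person-years.

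**Step 1: the rule applied literally.** Take a participant positive at swabs 1, 2 and 3 and negative from swab 4. No expected swab before swab 1 is missing, so the interval rule is not triggered and the count is exactly 3. The same holds at the other end for a run that reaches the last scheduled swab. If missing were meant to include time outside swabbing, the upper limit would be 3 plus an undefined number.

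**Step 2: share of carried-over infections before crossover.** Let d be the assumed proportion of each arm carrying earlier infection into swabbing. The share is 628d/(628d + 16) for vaccine and 302d/(302d + 28) for placebo. If the observed peak in such infections is k log10 too low (k = 1 to 3, assumed), the spurious vaccine-minus-placebo difference is -k x (difference in shares).

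| d | Vaccine share | Placebo share | Difference in shares | Spurious peak difference, k = 1 to 3 |
|---|---|---|---|---|
| 0.5% | 3.1/19.1 = 16% | 1.5/29.5 = 5% | 0.113 | -0.11 to -0.34 |
| 1% | 6.3/22.3 = 28% | 3.0/31.0 = 10% | 0.184 | -0.18 to -0.55 |
| 2% | 12.6/28.6 = 44% | 6.0/34.0 = 18% | 0.262 | -0.26 to -0.79 |

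The mITT counts serve as the base because mITT has already removed infections identified before dose 2; PP-ITT would add them back.

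**Step 3: simulation with no true vaccine effect on shedding.** Assumptions: twice-weekly swabs with 63% completed, efficacy 74.8% after dose 2 (Table S2), median clearance 12 or 21 days, infection hazard before dose 2 at 0.5 to 1 times the later hazard, first swab up to 28 or 60 days after dose 2. The true difference is 0 and the true count ratio is 1.
- Mean observed peak: about 4.5-4.8 log10 if positive at the first swab, 5.8-6.2 otherwise.
- PP-ITT before crossover, two doses minus none: -0.06 to -0.60 log10; count ratio 0.87-0.99.
- The same, keeping only episodes with a negative swab on both sides: -0.04 to +0.05; count ratio 0.98-1.01.
- PP-ITT over all follow-up by dose status: -0.12 to +0.31 log10. Requiring only a negative before the first positive: -0.10 to -0.03.
- PP-PAS before crossover, arm difference: 0.00 to +0.04.
- Still positive at the last swab: hardly moves the peak (about 0.1 log10) but shortens duration. In the PP-PAS runs this affected 12-18% of two-dose infections and none of the unvaccinated ones, because nearly everyone has crossed over by December.

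**Step 4: two ways of handling first-swab positives in 11.2.** With identical kinetics in both arms, the simulated vaccine/placebo count ratio was 0.94-0.98 under the plan, 1.03-1.13 if first-swab positives were right-censored, and about 1.00 if a preceding negative was required.

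**The case against.** Both endpoints are exploratory and touch no primary or secondary inference. Both analyses also run in PP-PAS and PP-PAS2, which rest on mITT, and the simulated arm bias in PP-PAS before crossover is about zero. SAP section 12 lists viral-load curve modelling for duration and peak, and section 11 expects ad hoc support. All of this stands and limits the weight of the point. It does not close the gap: first-swab positives remain in every set, PP-ITT is listed first, and section 12 gives no detail.

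A reader might infer more than the documents allow, in three ways.
- That the bias always lowers vaccine-arm viral load. Section 11.3 compares dose status, the PCR-positive sets have no cut at crossover, and over all follow-up the sign can reverse.
- That the effect can be sized from the PAS counts (13 and 21). PAS already excludes infections identified before dose 2, its first-swab positives may already be among those counts, and the counts stop at crossover dose 2.
- That 1196 enrolled less 957 in mITT, 239 or 20%, measures the carry-over. That group mixes prior infections with participants lacking a valid result, who cannot enter PP-ITT, and a past infection found by serology need not leave detectable RNA.

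It is also tempting to right-censor first-swab positives. They are a length-biased sample, since long infections are more likely to be caught in progress, and step 4 shows that this replaces one bias with another in the opposite direction.

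**Conclusion.** The gap is in the text. Followed as written, 11.2 and 11.3 score partly observed infections as complete, and PP-ITT adds infections that every mITT-based set removes. Before crossover, an assumed carry-over of 0.5-2% would make these 16-44% of vaccine-arm and 5-18% of placebo-arm positives. That is enough to mimic a vaccine effect on peak of a few tenths of a log10, with a smaller effect on duration. Over all follow-up the bias may mimic or mask a benefit. The carry-over rate, the peak deficit, the kinetics and the hazard before dose 2 are all assumptions; the documents give none of them, so the actual size cannot be read from the plan. The point is worth correcting in the SAP but bears only on exploratory results.

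**What to change.** 1. In 11.2 and 11.3 replace PP-ITT by the PCR-positive participants of mITT; keep PP-PAS and PP-PAS2. Section 11.4 already uses mITT, PAS and PAS2.
2. In both sections include only episodes with a negative SNIFF swab before the first positive, within a window stated in advance. Report first-swab positives separately, without right-censoring them.
3. In 11.2 treat a run still positive at the last swab before study end or withdrawal as right-censored at the observed count, and state how censored counts enter the Poisson likelihood, which the section leaves open.

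The cost is SAP wording and a flag derived from existing swab dates and results. A few episodes leave the main analysis and the intervals widen slightly. The simulations did not test the three changes together: the near-zero result before crossover came from requiring a negative on both sides, and a preceding negative alone left -0.10 to -0.03 log10 over all follow-up.

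### SAP 11.2 estimates the vaccine effect on shedding duration by randomised arm in sets that include infections detected after the placebo arm had been vaccinated

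*Supplement*

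**What the plan says.** The endpoint in SAP v2.0 section 11.2 is "Duration of shedding as indicated by RT-PCR as measured by the number of RT-PCR positive swabs". A swab missing between two positives is filled in as positive. Where swabs are missing next to the run of positives, "the endpoint will be interval censored with the interval being" the observed count up to that count plus the adjacent missing swabs. The model is stated in one sentence, "A Poisson model will be fit with randomization arm as the predictor of interest", with sex, age and comorbidities as covariates. The line naming the populations reads "Data sets: PP-ITT, PP-PAS, PP-PAS2".

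Section 3.1 defines the first of these sets as "All participants in the ITT population with SARS-CoV-2 RNA detected by RNA-RT-PCR as part of the SNIFF study". The other two are built the same way from PAS and PAS2. PAS and PAS2 limit when a participant enrolled, not how long follow-up counts, so none of the three sets stops at crossover.

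Other sections treat crossover differently:
- The endpoint table in SAP 2.2, like Protocol v4.0 section 3.3.3, asks for shedding duration in vaccinated people against placebo recipients.
- SAP 9.2 stops counting primary infections at the second crossover dose.
- SAP 11.3 analyses peak viral load in the same three sets, but with "vaccination status (no vaccine, 1 dose, 2 doses) as the covariate of interest, adjusted for age and sex".

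**The concern.** Protocol v4.0 section 2.1 says that crossover began on 10 August 2021 and that initial placebo recipients then receive two doses of vaccine. Section 6.5 has swabbing continue to 17 December 2021. A placebo-arm participant first positive in, say, November would usually be a vaccinated person, but 11.2 places that infection in the unvaccinated comparison group. Nobody in the vaccine arm changes status in the other direction, so the mixing affects one side only.

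Protocol 2.2.1 names magnitude and duration of shedding as proxies for transmission potential among vaccinated people who still become infected. A real shortening of shedding could look small or absent because part of the placebo group had the same vaccine.

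**Working it through.** The plan states no effect size, power or sample size for this analysis, so there is no figure of its own to reproduce.

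**Time after crossover.** Table S1 covers 1 June to 17 December 2021, which is 199 days. From 10 August to 17 December is 129 days, or 65% of that span. This is calendar time only; it does not give the share of infections.

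**Do the sets contain post-crossover infections?** Inclusion criterion 4 requires two doses of study product before enrolment. At enrolment a participant has therefore had either two vaccine doses or none. The one-dose category in 11.3 can then arise essentially only after the first crossover dose in the placebo arm. Section 11.3 uses the same three sets, so the SAP itself treats them as running past crossover.

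**Dilution formula.** A log-link Poisson model on arm alone estimates the ratio of arm means. Let *m* be the mean duration in unvaccinated infections, *R* the true vaccinated-to-unvaccinated ratio, and *f* the share of placebo-arm infections in vaccinated people.

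- Vaccine-arm mean: R·m
- Placebo-arm mean: (1−f)·m + f·R·m
- Expected ratio: R / ((1−f) + f·R)

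This assumes that vaccinated placebo-arm infections shed like vaccine-arm infections. Neither R nor f is in the documents; the values below are assumptions chosen to show a range.

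| f | R = 0.50 | R = 0.60 | R = 0.80 |
|---|---|---|---|
| 0.2 | 0.56 | 0.65 | 0.83 |
| 0.4 | 0.63 | 0.71 | 0.87 |
| 0.6 | 0.71 | 0.79 | 0.91 |
| 0.8 | 0.83 | 0.88 | 0.95 |

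For example, 0.60/(0.8 + 0.12) = 0.65 and 0.60/(0.4 + 0.36) = 0.79. With f = 0 the ratio returns to R. Sex, age and comorbidities do not carry vaccination status, so adjusting for them does not remove the mixing.

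**Would the dose-2 stop from 9.2 be enough?** Infections in Table S2 (results, used here only as a gauge):

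| Set and arm | Censored at dose 2 | Censored at dose 1 | Difference |
|---|---|---|---|
| PAS placebo | 21 | 10 | 11 (52%) |
| PAS vaccine | 13 | 5 | 8 |
| mITT placebo | 28 | 13 | 15 (54%) |

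About half of the placebo infections counted to dose 2 are added between the two crossover doses. These people had at most one vaccine dose, so 52% should not be read as a value of f for full vaccination.

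**The interval.** Table S3 reports that 63.0% of expected swab windows were received. In a simulation at that compliance (Poisson means of 4 and 2.4, positive counts only, so a ratio of actual mean counts of 0.65), about 83% of outcomes had at least one adjacent missing swab. The estimated ratio then depended on how the interval was used:

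- uncensored outcomes only: 0.61
- lower bound: 0.65
- interval-censored Poisson: 0.68
- midpoint: 0.71
- upper bound: 0.74

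An interval-censored, zero-truncated fit gave 0.63, but it estimates the ratio of the Poisson parameters (0.60), not of the mean counts.

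**The case against.** The strongest defence is that 11.2 is exploratory. SAP section 11 expects ad hoc support, and section 12 lists vaccination status as a time-varying covariate, analyses in calendar time, and modelling of shedding in days. Comparing by arm also keeps the two groups in the same calendar period, whereas vaccination status ties exposure to time and so to the change from alpha to delta. The last point stands and shapes the fix. The others show awareness, but section 12 describes those analyses only at a high level and leaves the 11.2 comparison as it is.

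A reader might go further than the documents allow in four ways.
- *That a Poisson model cannot use the intervals.* It can: the likelihood can sum over the stated interval. The gap is that 11.2 does not say so.
- *That ignoring the minimum count of 1 dilutes the effect, turning 0.50 into 0.61 for Poisson parameters of 3 and 1.5.* The actual mean counts in that case are 3/(1−e⁻³) = 3.16 and 1.5/(1−e⁻¹·⁵) = 1.93. Their ratio is 0.61, which is what an arm-only model of the stated endpoint should return. The simulation shows no fixed direction of bias from interval handling.
- *That the 34 PAS infections in Table S2 (21 + 13) are pre-crossover.* They are counted to crossover dose 2. Censored at dose 1 there are 15 (10 + 5).
- *That 11.3 is shown to confound vaccine with variant.* Post-crossover counts by vaccination status are not given, and SAP 3.2 plans repeat analyses in states where delta was dominant.

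**Conclusion.** The point holds for the arm comparison. Followed as written, 11.2 counts infections in vaccinated people as placebo infections. This departs from the contrast in SAP 2.2 and lacks the safeguards of 9.2 and 11.3. The direction is toward no effect, provided that vaccination shortens shedding and that crossover vaccinees shed like early vaccinees. The size is conditional: an assumed true ratio of 0.60 would be expected at 0.65 to 0.88 for f between 0.2 and 0.8, and the documents fix neither quantity. The unstated use of the interval is a second, smaller gap with no fixed direction. Primary and secondary results are not affected.

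**What to change.** In SAP 11.2, do one of the following:

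1. Keep the comparison by arm, but restrict it to infections first detected before crossover dose 1, with the dose-2 cut-off of 9.2 as a sensitivity analysis. This keeps the arms concurrent.
2. Use vaccination status at the first positive swab, as 11.3 does, together with a calendar-time or variant term. SAP 3.2 already warns that durability estimates are confounded by variant, and section 12 says time-varying vaccination models need variant information.

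In either case, state that the declared interval enters through an interval-censored likelihood for a count of at least 1, and say whether the reported ratio is of mean counts or of the underlying parameter.

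The cost is SAP wording and a different subset or model on data already held. The real price is precision. Option 1 leaves 15 infections in the PAS by the Table S2 counts. Option 2 keeps more infections but asks few of them to support extra terms, with a small one-dose group. Either estimate will be imprecise and should be reported as exploratory.
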